## Abstract

**Background:**

Polycystic ovarian syndrome (PCOS) is the most common endocrine disorder among women. Inappropriate eating behaviors are some of the most important risk factors for obesity in all age groups. Therefore, performing comprehensive culturally sensitive interventions for modification of eating behaviors as a useful affordable strategy seems necessary. So, this study aims to present a comprehensive interventional program for promoting eating behaviors in adolescent girls with PCOS.

**Methods:**

This study has a sequential exploratory mixed methods design including three sequential phases. The researcher represents eating behaviors among adolescent girls with PCOS using a qualitative approach. In the onset of the second phase, a comprehensive interventional program for promoting eating behaviors is designed for adolescent girls with PCOS. In this regard, in addition to qualitative studies, some related papers and texts are used. The suggested program of expert panel is approved based on prioritization guidelines. Then, in the third phase and after different stages of finalization of the program, its affectability is evaluated regarding improvement of eating behaviors in adolescent girls with PCOS.

**Discussion:**

Results of the present mixed methods study, by presenting an interventional culturally sensitive program for promoting eating behaviors in adolescent girls with PCOS, lead to the improvements of the health of young girls. If this program works, it can become one of the leading education guidelines for eating behaviors in adolescent girls with PCOS.

**Trial registration:**

IRCT20160224026756N6. Registered 18 Aug 2018.

## Plain English summary

Polycystic ovarian syndrome (PCOS) is a kind of hormonal imbalance among women of reproductive age. It would be indicated by symptoms such as obesity, hirsutism, menstrual cycle disorder and infertility, alone or together. In women and young girls with this syndrome, obesity is one of the pathophysiological principles; consequently, increased level of insulin in these patients might stimulate the production of ovarian androgens and hence, would lead to ovulation disorder and infertility. Inappropriate eating behaviors are one of the main causes of obesity. Since overweight and obesity have a principal role in causing, development of and complications caused by PCOS, appropriate weight and having healthy eating behaviors might significantly decrease the complications of PCOS among adolescent girls. The findings of this study are suitable sources for selecting the best intervention for promoting eating behaviors in adolescent girls with PCOS. This study is carried out by an exploratory sequential mixed qualitative-quantitative methods approach including three sequential phases. In this study, the researcher explains eating behaviors in adolescent girls with PCOS using a qualitative approach. In the onset of the second phase, a comprehensive interventional program is designed for promoting eating behaviors in these adolescent girls. In addition to qualitative study, some related papers and texts are studied. The suggested interventional program of expert panel is approved and validated based on prioritization guidelines. In the third phase and after different stages of finalization of the program, its affectability is evaluated regarding improvement of eating behaviors in adolescent girls with PCOS. It is expected that using the results of the present study and applying its suggested interventional program by adolescent girls, policymakers, health managements and families might have positive effects on administering and promoting healthy eating behaviors by adolescent girls with PCOS.

## Background

Polycystic ovarian syndrome (PCOS) was first explained 70 years ago [1, 2]. This syndrome is a kind of hormonal imbalance among women of reproductive age which its prevalence among the adults, according to the criteria by American National Institute, has been reported as 6.5%. PCOS is a heterogeneous disease; at one end of its spectrum, it shows morphological polycystic ovary symptoms in the ultrasound examination, and at the other end of the spectrum, it would be indicated by symptoms such as obesity, hyperandrogenism, menstrual cycle disorder and infertility, alone or together. In women and young girls with this syndrome, obesity is one of the pathophysiological principles; consequently, increased level of insulin in these patients might stimulate the production of ovarian androgens and hence, would lead to ovulation disorder and infertility [3, 4]. Obesity could aggravate all of the infertility and metabolic problems of this syndrome [5, 6]. According to string evidences, PCOS would onset during adolescence but, unlike the adults, its diagnosis is difficult among the adolescents [7]. The prevalence of this disease among 11–19 years old girls, based on diagnostic criteria, has been reported as 1.8–15% [8].

The global prevalence of obesity among adolescents is 12 to 20% [9]. Inappropriate eating behaviors are one of the main causes of obesity [10, 11]. Nutritional habits usually form during adolescence and continue to adulthood, so they could affect eating behaviors and the intake of the nutrients. Since overweight and obesity have a principal role in causing, development of and complications caused by PCOS, according to studies, appropriate weight and having healthy eating behaviors might significantly decrease the complications of PCOS among adolescent girls [6]. So, weight loss and lifestyle modification are defined as the first line treatments for this syndrome [12]. So, various low-calorie diets with different combinations, including macronutrients, have been suggested for weight loss of obese people. But the existing information about the condition of adolescents with PCOS and their nutritional behaviors is so limited [13] and no studies have been conducted in this field in Iran. Considering the long-term and life-threatening complications of PCOS, including metabolic, cardiovascular and especially infertility, and also imposing heavy costs on individuals and the society, the need for modification of nutritional behaviors, as a useful affordable strategy, seems necessary. Therefore, the aim of the present study is to present a comprehensive interventional program for promoting eating behaviors in adolescent girls with PCOS.

### Objectives

Objectives of each phase are as the following:

### Objectives of the first phase: Qualitative study

Explaining eating behaviors in adolescent girls with PCOS.

### Objectives of the second phase: Program design

Designing a primary intervention program based on extracted data from qualitative phase and review.

### Objectives of the third phase: Quantitative study

Explaining affectability of the comprehensive interventional program for promoting eating behaviors in adolescent girls with PCOS.

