#### Research population

The targeted population for quantitative study is all adolescent girls with PCOS referred to gynecology training clinics covered by Shiraz University of Medical Sciences.

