#### Sample size

Sample size will be 36 participants in each group considering 95% confidence interval, 80% trial power, S = 0.1–0.25 and 10% loss.

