#### Sampling method

This clinical trial has one intervention group and one control group. After identifying the clinics covered by Shiraz University of Medical Sciences, four gynecology training clinics will be selected non-randomly. Afterwards, 18 adolescent girls with PCOS with inclusion criteria will be selected from each center via convenience sampling method.

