#### Exclusion criteria

Unwillingness to continue cooperation during the trialUse of certain dietary patterns during studyFailure to receive 50% of the intervention for any reason

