#### The implementation method

The researcher will implement the designed program after obtaining the necessary coordination with authorities of four gynecology training clinics covered by Shiraz University of Medical Sciences. This is done by referring to the gynecology training clinics and presenting a letter of introduction to the authorities of those centers regarding research objectives. After that, the researcher will be allowed to access to phone numbers of adolescent girls with PCOS and call her in order to explain research objectives and invite them to participate in the research. If they are willing to cooperate, and have all the inclusion criteria, they will be selected by convenience sampling method with their informed consent.

Adolescent girls^,^ knowledge, attitude, subjective norms, perceived behavioral control, behavioral intention and eating practice (behavior) will be considered as the suggested outcomes. Before intervention, the questionnaires will be filled by them in each of the two groups. Furthermore, the questionnaires will be refilled by adolescent girls with PCOS three months after the intervention.

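### The exclusion for receiving less than half of the programme in effect thins the intervention arm only, so the comparison no longer estimates the effect in girls as enrolled and probably, though not certainly, favours the programme

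*Protocol article*

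**What the plan says.** - **Aim.** Objectives of the third phase: "Explaining affectability of the comprehensive interventional program for promoting eating behaviors in adolescent girls with PCOS".
- **Population.** Under Research population the plan states: "The targeted population for quantitative study is all adolescent girls with PCOS referred to gynecology training clinics covered by Shiraz University of Medical Sciences". Neither statement is limited to girls who take the programme up.
- **Arms.** Sampling method: "This clinical trial has one intervention group and one control group". Neither this section nor The implementation method describes any sessions or programme for controls.
- **The rule.** Eligibility at entry is dealt with under Inclusion criteria. The separate Exclusion criteria hold three items that arise during the trial: no longer wishing to cooperate, following certain dietary patterns, and failure "to receive 50% of the intervention for any reason".
- **Follow-up.** The implementation method has all questionnaires completed before the programme, and then "the questionnaires will be refilled by adolescent girls with PCOS three months after the intervention".
- **Sample size.** The basis is given as: "Sample size will be 36 participants in each group considering 95% confidence interval, 80% trial power, S = 0.1–0.25 and 10% loss".
- **Analysis.** Data analysis lists t-tests, rank tests, categorical tests and ANCOVA for intervening variables. It does not name the covariates, and it says nothing that keeps excluded girls in the comparison.

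**The concern.** The third exclusion depends on how much of the programme a girl received. A control has nothing described of which she could receive less than half, so the rule reaches one arm only. The other two exclusions can act in both arms.

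However the groups were formed, the remaining intervention girls are then a selected subset, and no equivalent selection on receipt is made among controls. The wording covers every reason, so it includes girls who stopped because the programme did not suit them. That is part of the effect the trial sets out to measure.

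The outcomes are self-completed scores for knowledge, attitude, norms, perceived control, intention and eating practice. A girl's motivation may well influence both her attendance and her scores. The Discussion says that a working programme could become a leading education guideline for these girls, and for that use the effect in all enrolled girls is what counts. If excluded girls are not asked for the three-month questionnaire, no later analysis plan can recover their data.

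**Working it through.** **1. The plan's own figure.** The base sample size cannot be reproduced, because no detectable difference is given. The loss step is consistent with 32 evaluable girls per group: 32 / (1 − 0.10) = 35.6, rounded up to 36. The standardised difference that 32 per group detects with 80% power (two-sided 5% assumed, normal approximation) is (1.960 + 0.842) × √(2/32) = 0.70 SD. This serves only as a yardstick.

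**2. Ceiling on the bias when the programme has no effect.** The article gives neither of the two inputs, so both are assumptions:
- q, the share of the intervention arm below 50% receipt: 10–30%, which is 3.6 to 10.8 of 36 girls;
- r, the correlation of motivation with the three-month score: 0.3–0.5.

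Suppose that exactly the least motivated share q is removed from the intervention arm, and that follow-up scores are compared without baseline adjustment. The spurious difference is r × φ(z_q) / (1 − q), where φ is the standard normal density and z_q the normal quantile at q. The factor φ(z_q) / (1 − q) is 0.1755/0.9 = 0.195 at q = 10%, 0.2800/0.8 = 0.350 at 20%, and 0.3477/0.7 = 0.497 at 30%. The error rates come from simulated t-tests, 36 per group before removal.

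| q | Difference, r = 0.3 | Difference, r = 0.5 | Two-sided error, r = 0.3 | Two-sided error, r = 0.5 |
|---|---|---|---|---|
| 10% | 0.058 SD | 0.097 SD | 5.9% | 7.3% |
| 20% | 0.105 SD | 0.175 SD | 6.8% | 10.6% |
| 30% | 0.149 SD | 0.248 SD | 8.9% | 16.3% |

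Against 0.70 SD this is 0.058/0.70 = 8% to 0.248/0.70 = 35%.

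**3. Softer assumptions.** Same q and r, with an assumed baseline-to-follow-up correlation of 0.6 and motivation related equally to both scores (simulation):

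| Setting | Spurious difference | Two-sided error |
|---|---|---|
| Exact removal, unadjusted | 0.06–0.25 SD | about 6–16% |
| Exact removal, baseline as ANCOVA covariate | 0.02–0.11 SD | about 5–8% |
| Attendance correlated 0.5 with motivation, unadjusted | 0.03–0.12 SD (half the first row) | about 5–8% |
| Both | 0.01–0.05 SD | about 5–6% |

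At r = 0.1 with exact removal and no adjustment, the difference is 0.02–0.05 SD. At r = 0 it is nil. At r = −0.3 it reverses, to between −0.06 and −0.15 SD.

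**4. When the programme does work.** Suppose it gives 0.70 SD to girls who receive at least half and nothing to the rest. The effect in all enrolled girls is 0.70 × (1 − q), and power with 36 per group and full follow-up is Φ(effect × √18 − 1.96).

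| q | Effect in all enrolled | Power, 36 per group | Per group for 80% |
|---|---|---|---|
| 10% | 0.63 SD | 76% | 40 |
| 20% | 0.56 SD | 66% | 50 |
| 30% | 0.49 SD | 55% | 66 |

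At q = 20%, reporting 0.70 SD as the effect in enrolled girls overstates it by 0.70/0.56 − 1 = 25%. This part needs no link between motivation and scores; it follows from leaving out girls who gain nothing.

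**The case against.** Several objections are fair, and they limit the point.

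- **Controls can be lost too.** A reader might infer that attenders are compared with all controls. The document does not support that: the exclusions for unwillingness to continue and for certain dietary patterns are not confined to one arm. The imbalance is the net difference between arms, which is unknown.
- **One-sidedness is inferred.** The article does not say in so many words that the rule spares controls. The inference is sound, since nothing is described that they could fall short of.
- **Direction is not fixed.** Missed sessions may have causes unrelated to motivation. A reader might take bias towards the programme as certain; it is only the expected direction.
- **The largest figures are a corner case.** They need exact removal of the least motivated girls and no baseline adjustment. Baseline scores are collected and ANCOVA is planned, so the bias could be well below the ceiling. Because the covariates are not named, adjustment for baseline score cannot be taken as given.
- **The loss allowance.** A reader might infer that the rule breaks the 10% allowance. That would need more than 10% removed, and no attendance rate is given.
- **Removal from analysis is inferred.** The section does not say that data are discarded, and analysis sets are often left to a fuller document. What stands is that the article itself states an exclusion tied to receipt of the programme, and nothing in it keeps these girls in follow-up or analysis.
- **The objective is loosely worded.** It does not say outright whether the effect is sought in all enrolled girls or in recipients. Read with the target population, the first is the natural meaning. The objective itself is not at fault; the exclusion rule is.

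**Conclusion.** The point stands against the third item of the Exclusion criteria. Followed as written, it makes membership of the comparison depend on receipt of the programme, in effect in one arm only, so the result no longer estimates the effect in girls with PCOS as enrolled.

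Bias towards the programme is likely but not certain. With no true effect, 10–30% removed and correlations of 0.3–0.5, it is at most about 0.06–0.25 SD (two-sided error about 6–16%), and clearly less with baseline ANCOVA or when attendance only partly reflects motivation. All these inputs are assumptions.

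The stronger conclusion, that an ineffective programme would be found to work, is not supported: under the softer settings the error rate stays near 5%. The rule still needs changing, because the population it leaves is not the one the aim and target population describe, and follow-up data not collected cannot be recovered.

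**What to change.** - **Exclusion criteria (quantitative phase):** delete receipt of less than half the programme as a reason for exclusion.
- **The implementation method:** state that girls are invited to the three-month questionnaires however much of the programme they received.
- **Data analysis:** state that every girl is analysed in the group to which she was assigned, using ANCOVA with the baseline score of the same outcome as covariate. Report attendance, and give the result among girls with at least 50% attendance only as a labelled supplementary analysis.

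**Cost.** The text changes are a few sentences and no visit is added, since the questionnaire is already scheduled. The statistical cost should be stated openly. If poor attenders gain little, the estimated effect and the power fall: with 36 per group, power is 76%, 66% or 55% when 10%, 20% or 30% gain nothing from a 0.70 SD programme, and 40, 50 or 66 per group would restore 80%. Those powers are for an unadjusted comparison. The baseline covariate wins some back: at the assumed correlation of 0.6 the residual SD is √(1 − 0.6²) = 0.8, so an effect of 0.56 SD counts as 0.56/0.8 = 0.70 SD, which offsets the dilution at 20%. The sponsor should say what non-attendance it expects and check the sample size against it.

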## Methods/ design

The present study is a mixed method interventional study with a sequential design (qualitative-quantitative) including three sequential phases. The researchers use a qualitative approach to explain eating behaviors in adolescent girls with PCOS and the required strategies for their healthy nutritional behavior. For this end, they analyze experiences of the participants. In this phase, the data are collected via semi-structured individual in-depth interviews, focused group discussions, and field noting. The qualified participants are selected with a purposeful approach and with maximum variety. Simultaneous with data collection, the interviews will be analyzed with a conventional content analysis method. Sampling and coding will be continued until saturation occured. After saturation and at the end of interviews, the researcher enters the second phase of the study in which a comprehensive program will be designed for promoting eating behaviors in adolescent girls with PCOS. For this end, a literature review of papers and texts will be used in addition to the results of qualitative study. Then, based on the results of the qualitative study, literature review and holding expert panel, a comprehensive program will be designed for modification of healthy eating behaviors among adolescent girls with PCOS. Then, the suggested program will be validated based on prioritization guidelines. In the third phase and after different stages of finalization of the program, its affectability is evaluated regarding improvement eating behaviors in adolescent girls with PCOS. The collected data will be processed by SPSS Version 20.0 software and will be analyzed with descriptive-analytic statistical methods (Fig. 1).

**Fig. 1 Fig1:**
[figure not shown]
Study visual diagram

### First phase: Qualitative study

The first phase of this study is designed for answering the question of: “What do you eat during the day” from adolescent girls with PCOS or “Do usually adolescent girls with PCOS have problems in the food dietary?” from the viewpoint of other participants. This study will be carried out using a qualitative content analysis method.

### Participants in the qualitative phase

Research community of the first phase consists of adolescent girls with PCOS and their parents. Other participants of this phase of the study will be midwives, gynecologists, endocrinologists and dietitians and also authorities of the adolescents and youth health unit of the health centers of Shiraz, Iran.

### Sampling method

In this phase of study, participants are selected with a purposeful sampling method. They are selected based on maximum variety in age, education, job, marriage status and duration of the diagnosis of disease.

### Inclusion criteria for participants

Being an adolescent girl from 15 to 21 years old (for diagnosis and definition of PCOS, at least two years must be passes from menarche) [14].Willingness to participate in the study and obtaining informed consent from the adolescent and her parents (in cases of younger than 18 years old)Overweight or obese adolescent girls with PCOS that their diagnosis of PCOS has been confirmed by a gynecologistNot having a history of diagnosed major mental problems undergoing drug treatmentsNot having any chronic diseases (cardiovascular diseases, diabetes, renal diseases, etc.), which requires special diet prescribed by a physician

### Research environment

The participants are accessed through the health centers and hospitals covered by Shiraz University of Medical Sciences and gynecologists and midwives offices. The interviews will be done in the location and time selected by the participants for their comfort and ease.

### Data collection process

After obtaining permission from Shiraz University of Medical Sciences, the researchers will select the participants by referring to research environments. In the qualitative phase, data collection methods include individual, in-depth, open, and semi-structured interviews along with focused group discussions and field noting. The interviews will be recorded. After explaining objectives and methodology of the study, the researcher will receive written consent regarding participation in the research, further interviews, and recording the interviews. Location of the interviews will be selected by the participants. In semi-structured individual interviews, the first interviews are done with the aim of understanding possible and unpredictable issues. The general questions of semi-structured interviews are identified based on the resulted information. At the end of each interview, the narrative will be transcribed immediately, and data analysis will be done simultaneously with data collection. Data collection continues until saturation - as long as no new code or data is extracted. At this point, data saturation and adequacy will be verified.

